### Study design

Data collection will be carried out at the Center for Studies and Assistance in Physiotherapy and Rehabilitation (CEAFIR) of FCT/UNESP, respecting the time from 17 to 22 h. All procedures will be performed under standard conditions (temperature: 21–23 °C; relative humidity: 40–60%). Each participant will attend the clinic for five consecutive days. Initially, participants will be assessed for anthropometric characteristics, using a scale (Tanita BC 554, Iron Man/Inner, Arlington Heights, IL, USA) and a stadiometer (Sany - American Medical do Brasil, São Paulo, Brazil) from which the body mass index (BMI) will be calculated.

After these initial procedures, the TOP evaluation will be carried out. After a 10-minute rest, baseline outcome assessments will be performed. Initially, CK and blood lactate will be collected, followed by the application of the scales of perception of recovery and muscle pain and the pain threshold. In the supine position, the participant will rest for 10 min before the ultrasound, myotonometry, and bioelectrical impedance (BIA) evaluations are performed. Subsequently, MVIC will be evaluated. Next, the participants will perform the previously randomized 40-min IPC protocol. Evaluations will be carried out immediately after the IPC protocol of all analyzed outcomes except for ultrasound. The same order of execution of the evaluations will be maintained. Thereafter, EE will be initiated, and immediately after the end of the EE, all outcomes will be collected again. Subsequent visits will be carried out 24, 48, 72, and 96 h after the EE, in which the same outcomes mentioned above will be collected, maintaining the same order of execution of the evaluations. The study design is outlined in Fig. 2.

**Fig. 2 Fig2:**
[figure not shown]
Study design

### Total occlusion pressure determination

After assessing the anthropometric parameters, the participants will be asked to lie down for 10 min [35]. All participants will be instructed to avoid strenuous exercise and alcohol intake within 48 h of the TOP assessment.

For the determination of TOP, a transducer with Doppler equipment (DV-2001; Medpej, Ribeirão Preto, São Paulo, Brazil) will be used, which will be positioned over the posterior tibial artery to capture the auscultatory pulse located at the average distance between the medial malleolus tibia and Achilles tendon. A blood pressure cuff will be attached to the participant's thigh close to the region of the inguinal crease of the dominant member [34] and will then be inflated to the point where the auscultatory pulse of the tibial artery is interrupted. TOP will be defined as the pressure at the moment when the arterial pulse is abolished, indicated by the absence of an auscultatory signal.

The vascular occlusion will be performed using an adapted blood pressure cuff (nylon, velcro, 175 mm wide and 920 mm long, JPJ - Hospital Materials Industry, São Paulo, Brazil). We opted for a wider cuff, as it has been proven that the width of the cuff has a great influence on the pressure required to achieve total blood flow restriction [36].

### Ischemic preconditioning protocol

The IPC protocol will be applied to the inguinal region of the dominant limb with the participants relaxed and comfortably positioned in the supine position. The same cuff used to determine TOP will be used and the protocol will consist of four cycles of total ischemia (TOP determined individually) of five minutes, followed immediately by four cycles of five minutes of vascular reperfusion (0 mmHg), totaling 40 min, as shown in Fig. 3.

**Fig. 3 Fig3:**
[figure not shown]
IPC protocol

To perform the IPC protocol, one of the study groups will use 40% more than the TOP, according to the study by Lopes et al. [37], the pressure at which the blood flow stops passing to the tibial artery varies from 140 to 160 mmHg and most studies performing IPC use pressures between 200 and 220 mmHg; thus, the values are corresponding [37]. The other study group will use the exact TOP, since at this value there is an absence of blood flow.

### Placebo preconditioning

Placebo preconditioning will be performed on the dominant thigh with the same cuff, similar to the IPC protocol described above (Fig. 3), but with four cycles of 5 min of placebo occlusion (10 mmHg), alternating with four cycles of 5 min of reperfusion (0 mmHg) [38, 39].

It should be mentioned that in the three study groups, participants will be previously informed that the applied occlusion pressure will be sufficient to improve performance and avoid muscle damage. In addition, all procedures will be performed individually, to prevent participants from talking to each other about the compression generated by the cuff.

### Eccentric exercise protocol

The EE will be performed on an isokinetic dynamometer (Biodex System 4 Pro, New York, NY, USA) for the knee extensor muscles of the dominant limb. Initially, five submaximal knee extension contractions will be performed for familiarization. Before each repetition, the dominant leg will be positioned at 30° of knee flexion. The participant will be instructed to perform a knee extension, while the dynamometer, with its resistance, returns the leg to 90° flexion, at a speed of 60°/s (1.04 rad/s) executing a range of movement of 60° (30–90° of knee flexion).

The protocol is based on the study by Machado et al. [25], starting 5 min after familiarization and consisting of 5 sets of 15 maximum eccentric contractions of knee extension, with 30 s of rest between sets, totaling 75 repetitions. The speed and range of movement will be similar to the familiarization and verbal encouragement will be given throughout the protocol. According to the authors, this protocol is capable of promoting muscle damage [25].

### Primary and secondary outcomes and assessment points

Primary outcomes will be related to muscle damage and muscle function through the quantification of creatine kinase, blood lactate, MVIC, and muscle thickness. In addition, there will be four measures of secondary outcomes: assessment of pain and pain threshold, assessment of recovery perception, myotonometry (muscle tone, stiffness, and elasticity), and electrical bioimpedance (resistance, reactance, and phase angle). All outcomes will be collected at the initial assessment with the exception of the perception of recovery, and immediately and 24, 48, 72, and 96 h after the end of the EE. Ultrasonography will not be performed immediately after the exercise.

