#### Blood lactate concentration

To assess the participant’s blood lactate concentration, 25 mL of blood will be collected from an ear lobe capillary. Heparinized capillaries and polyethylene Eppendorf tubes (1.5 mL) containing 50 μL of sodium fluoride (NaF - 1%) will be used. The analyses will be performed on a lactimeter (YSI, Yellow Springs - 1500) [41] and the lactate values will be expressed in mmol/L. The lactate will be collected at the following moments: pre IPC protocol, pre EE, immediately after the end of EE, and in the 1st, 3rd, 5th, 7th, 9th, 11th, 13th, and 15th min, and 24 h, 48 h, 72 h, and 96 h after the intervention. The samples will be stored in a refrigerator with a temperature of 1 °C to 7 °C until their analysis.

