#### Muscle thickness

The evaluation of the muscular structure will be carried out using ultrasound images of the participant’s dominant lower limb, which will be captured using Siemens Sonoline Sienna equipment (Issaquah, WA, USA), together with a linear matrix transducer (48 mm, 7, 5 MHz) to determine the thickness of the rectus femoris (RF) and vastus lateralis (VL) muscles. Anatomical reference points and skin marks will be drawn on transparent sheets to ensure similar positioning of the ultrasound transducer in the same location in the evaluations.

The images will be taken between the midpoint of the greater trochanter and the lateral condyle of the femur [46]. The ultrasound transducer will be covered with water-soluble transmission gel and positioned perpendicular to the skin over the RF and VL and oriented parallel to the muscle fascicles [46]. The alignment of the transducer will be considered adequate when several fascicles can be drawn without interruption through the image [46].

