#### Sample calculation

The sample calculation was performed based on the study by Bailey et al. [54], using the CK variable, since this variable expresses the amount of muscle protein in the blood representative of indirect muscle damage. The G*Power 3.1.9.7 software was used. Considering the standard deviation in the CK concentration of 200 μL, using a two-tailed hypothesis test with 80% test power and 5% significance level, a sample size of 16 participants per group was stipulated. Predicting sample loss, 4 participants per group were added totaling 80 participants. To increase the participants’ adherence to the intervention, telephone contact will be made daily to encourage them to remain in the study, and thus avoid losses. In case of discontinuity or withdrawal, the intention to treat will be used.

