### Statistical analysis

The normality of the data will be verified by the Kolmogorov Smirnov test. If normality is detected, the sample characterization variables will be presented as mean and standard deviation, if not, as median and interquartile range. To compare the characterization of the sample, one-way ANOVA with Tukey’s post test or Kruskal-Wallis with Dunn’s post test will be used depending on the normality of the data.

The comparisons of the outcomes between the four groups studied and the moments will be performed using the technique of analysis of variance for repeated measures model in the two-factor scheme, which will provide information on the effects of time, group, and interaction. The repeated measurement data will be checked for sphericity violation using Mauchly’s test and the Greenhouse-Geisser correction will be used when the sphericity is violated. For moment analysis, Bonferroni’s post-test for parametric distribution or Dunn’s post test for non-parametric distribution will be used and the analysis between the groups will be performed using one-way ANOVA or the Kruskal-Wallis test.

In addition, the effects of the groups studied will be verified for all the outcomes assessed by calculating the effect size (ES) using Cohen’s *d*, considered as “null” (< 0.2), “small” (≥ 0.2), “moderate” (≥ 0.6), “large” (≥ 1.2), or “very large” (≥ 2.0) [55].

An intention-to-treat analysis will be performed using the patient’s most recent assessment in case of withdrawals or absence of data. The level of significance will be p < 0.05 for all tests. The statistical program SPSS (version 24.0) (SPSS Inc., Chicago, IL, USA) will be used for the analyses.

The external evaluator will enter the data into the database for screening, randomization, and statistical analysis purposes. Double data entry in electronic format will be used. Data integrity will be monitored by regularly scrutinizing data files for omissions and errors. Participants will be given an anonymous study ID to protect confidentiality, and only study investigators will have access to the final trial data set. The spreadsheets containing the raw numeric data of the data generated in this study will be stored in its entirety initially on two external hard drives and two online clouds. Any data required to support the protocol can be supplied on request.

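### Four unranked primary outcomes (five variables) are all tested at p < 0.05, with no control of error across outcomes or between-group tests

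*Protocol article*

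**What the plan says.** - **Primary outcomes.** The section headed Primary and secondary outcomes and assessment points names four without ranking them: "Primary outcomes will be related to muscle damage and muscle function through the quantification of creatine kinase, blood lactate, MVIC, and muscle thickness". It also fixes no primary moment.
- **Fifth variable.** Under Muscle thickness, the ultrasound images serve "to determine the thickness of the rectus femoris (RF) and vastus lateralis (VL) muscles".
- **Moments.** The outcomes section lists five post-exercise moments (immediately, 24, 48, 72 and 96 h), with no immediate ultrasound. Blood lactate concentration adds samples "in the 1st, 3rd, 5th, 7th, 9th, 11th, 13th, and 15th min".
- **Analysis.** Under Statistical analysis, each outcome gets a two-factor repeated-measures analysis of variance (time, group, interaction). Bonferroni or Dunn post-tests are attached to the moments, and "the analysis between the groups will be performed using one-way ANOVA or the Kruskal-Wallis test". The threshold is fixed: "The level of significance will be p < 0.05 for all tests".
- **Sample size.** Under Sample calculation, the trial is sized "using the CK variable, since this variable expresses the amount of muscle protein in the blood representative of indirect muscle damage". The result is given as "using a two-tailed hypothesis test with 80% test power and 5% significance level, a sample size of 16 participants per group was stipulated".

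**The concern.** A primary outcome is the result by which the trial will be judged. Here any of five variables, at any of several moments, can supply that result, and each is tested at the full 5%. No rule says which one decides, or how many must succeed. A significant between-group difference in, say, vastus lateralis thickness at 72 h could be reported as a positive primary result while CK, the variable that sized the trial, shows nothing.

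The single threshold is a stated rule, so this is more than a detail left to an analysis plan. Following the article as written inflates the false-positive rate on the primaries.

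The Introduction also hypothesises that preconditioning protects and that the higher pressure protects more. Between groups, the article names only a four-group omnibus test. That test alone cannot say whether preconditioning beats placebo or whether IPC-40% differs from IPC-TOP.

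**Working it through.** **1. The plan's own figure.** The inputs are two-sided 5%, 80% power and the statement "Considering the standard deviation in the CK concentration of 200 μL". No CK difference is given, so 16 per group cannot be reproduced from the article.
- Working backwards: difference = 200 × √(2/16) × (1.960 + 0.842) = 198, about one standard deviation.
- Assuming d = 1: n = 2 × (1.960 + 0.842)² / 1² = 15.7, so 16 per group. The t-test version gives 17.
- The allowance agrees: 16 + 4 = 20 per group, and 20 × 4 = 80.

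The stated size therefore fits one two-group comparison of one variable at an unadjusted 5%, with d near 1.

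**2. One test per primary.** If the tests are independent and nothing works, the chance of at least one p < 0.05 is 1 − 0.95^k.
- Four outcomes: 1 − 0.95^4 = 18.5%.
- Five variables: 1 − 0.95^5 = 22.6%.

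**3. Counting the post-exercise between-group tests.**

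| Count | CK | Lactate | MVIC | RF | VL | Total | If independent |
|---|---|---|---|---|---|---|---|
| Outcomes-section schedule | 5 | 5 | 5 | 4 | 4 | 23 | 1 − 0.95^23 = 69.3% |
| With the eight early lactate samples | 5 | 13 | 5 | 4 | 4 | 31 | 1 − 0.95^31 = 79.6% |

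The second Study design section says all outcomes are collected again immediately after exercise, while the outcomes section excludes ultrasound then. Counting an immediate scan turns 23 into 25 (72.3%).

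**4. Allowing for correlation.** Repeated measures on one person are correlated, so the independent figures are too high. Simulation used four groups of 20, no true effect, and a one-way analysis of variance at each moment with no gate. The correlations are assumptions.
- 23 tests: about 37-63% for within-outcome correlation 0.5-0.9.
- 31 tests: about 38-72% over the same range.
- The rate falls as correlation rises. With 23 tests and cross-outcome correlation set at 0 to 0.6 times the within-outcome value, it is 58-63% at 0.5, 48-56% at 0.7, 40-51% at 0.8 and 32-43% at 0.9. The 32% comes from the strongest cross-outcome correlation tried.

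**5. Power if all primaries stay.** Two-group comparison, assumed d = 1, normal approximation: power = Φ(√(n/2) − z).

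| Threshold | z | n = 16 | n = 20 |
|---|---|---|---|
| 0.05 / 4 = 0.0125 | 2.498 | Φ(2.828 − 2.498) = 63% | Φ(3.162 − 2.498) = 75% |
| 0.05 / 5 = 0.01 | 2.576 | Φ(2.828 − 2.576) = 60% | Φ(3.162 − 2.576) = 72% |

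Restoring 80% power under Bonferroni over four needs 23 per group (24 by t-test). Over five it needs 24 (26 by t-test).

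**The case against.** **The one-way tests may be follow-up.** The main model is one repeated-measures analysis per outcome, and the one-way tests are listed after it, beside the post-tests for moments. Counted only after a significant group or interaction effect for that variable, the simulated rate for the 31 tests is 22-30%. Counted only after a significant interaction, it is 4-13%. This is a fair reading, but the article states no such gate. If the interaction test itself is what counts as the primary result, the 19-23% applies.

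**The larger count leans on lactate.** Thirteen of the 31 tests are lactate, eight of them within 15 minutes of exercise. The schedule in the outcomes section gives 23. This stands, and it is why a range is reported.

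**Error is not wholly uncontrolled.** A reader might infer that the plan has no error control at all. That goes too far, because the Bonferroni or Dunn post-tests cover comparisons between moments. They do not reach the primaries as a set or the between-group tests.

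**Contrasts may be in the full plan.** An article commonly leaves pairwise contrasts to the full protocol or analysis plan, and this one promises Cohen's d for all outcomes. So it cannot be concluded that the dose hypothesis will go untested. What can be said is that the between-group test the article names does not answer it, and an effect size is not a test.

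**Conclusion.** The concern holds. Four co-equal primaries (five variables), a fixed 0.05 for every test and a sample size built on CK alone leave the primary false-positive rate above 5%, with no rule for which result decides.

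The rate is 18.5-22.6% with one independent test per primary. It is roughly 37-72% if each of the 23 to 31 post-exercise between-group tests stands alone without a gate. That upper range rests on assumed within-outcome correlations of 0.5-0.9.

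A reader might go further and say that a false primary finding is more likely than not. The documents do not support that. It is true at moderate correlation, but the rate falls below one half at 0.9, and it is far below one half if each primary is judged by one test. The article gives no correlations and does not say whether the one-way tests stand alone.

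**What to change.** **Preferred.** Name CK, the outcome that sized the trial, as the single primary. Specify one between-group test at 5%, for example one group-by-time test or one baseline-adjusted post-exercise summary. Relabel lactate, MVIC and thickness as secondary.

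**Alternative.** Keep all primaries, reduce each to one fixed test, and apply Holm across them: four tests if rectus femoris and vastus lateralis are combined, otherwise five. Holm controls the error only once each outcome has a single test. Applied to outcomes still tested at several moments, it does not.

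**In either case.** State that one-way tests at individual moments are follow-up only, with adjustment. Name the between-group contrasts that answer the Introduction's hypothesis (preconditioning versus placebo, IPC-40% versus IPC-TOP) and how multiplicity between them is controlled. If they are tested in fixed order, the second goes untested when the first fails, so the order should reflect that pressure is the study's stated aim. Reconcile the two statements on ultrasound immediately after exercise.

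**Cost.** Under the first option, three outcomes lose confirmatory status. Under the second, power falls below the stated 80%: about 75% at 20 and 63% at 16 per group with Bonferroni over four, assuming d = 1; Holm is somewhat better. Recruitment is reported as under way, and the article commits to notifying the ethics committee and updating the registration for any protocol change, so both steps are needed.

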### Details of procedures

#### Creatine kinase

Plasma CK concentration will be obtained by means of 32 μL of capillary blood collected from the digital pulp. This puncture will take place by means of a lancet with automatic trigger, after cleaning the location with 95% ethyl alcohol and drying with cotton. The blood sample will be drained into a heparinized capillary tube and then pipetted into a reactive CK strip for analysis on the Reflotron Plus System (Roche Diagnostics, Mannheim, Germany) using the reflection photometry method at 37 °C (test temperature). The test strips will be kept at a storage temperature of 2 to 8 °C, according to the manufacturer's instructions. The Reflotron System method allows fast and reliable measurement of CK levels [40].

#### Blood lactate concentration

To assess the participant’s blood lactate concentration, 25 mL of blood will be collected from an ear lobe capillary. Heparinized capillaries and polyethylene Eppendorf tubes (1.5 mL) containing 50 μL of sodium fluoride (NaF - 1%) will be used. The analyses will be performed on a lactimeter (YSI, Yellow Springs - 1500) [41] and the lactate values will be expressed in mmol/L. The lactate will be collected at the following moments: pre IPC protocol, pre EE, immediately after the end of EE, and in the 1st, 3rd, 5th, 7th, 9th, 11th, 13th, and 15th min, and 24 h, 48 h, 72 h, and 96 h after the intervention. The samples will be stored in a refrigerator with a temperature of 1 °C to 7 °C until their analysis.

#### Perception of recovery

The perception of recovery of the lower limb submitted to the EE protocol will be assessed using a 10-point Likert scale, where 1 indicates “not recovered” and 10 “fully recovered” [25]. The scale will be presented to the participants and so that they are not influenced by the researcher, they will answer the question: “From 1 to 10 points, how do you rate the perception of recovery felt in your lower limb at this moment?” [25, 42]. This scale will be applied immediately after the end of the EE, and 24, 48, 72, and 96 h after the intervention.

#### Muscle pain and pain threshold

Muscle pain will be measured using the visual analog scale (VAS). Participants will be asked to rate their exercise-induced leg pain, on the scale, which ranges from 0 “no pain” to 10 “extreme pain” [43].

To assess the pain threshold, a pressure algometer will be used, which is a reliable and validated instrument (FPX 50/220; Wagner instruments, Greenwich, CT, USA) [44]. The pressure algometer will be applied 4 cm above the base of the patella, 15 cm below the antero-superior iliac spine (ASIS), midpoint between the patella and the antero-inferior iliac spine (AIIS), and 2 cm medial and 2 cm lateral in relation to the midpoint. The pain threshold will be defined in kgf and will not exceed 2.55 kgf, as suggested by Jӧnhagen et al. [45].

#### Muscle thickness

The evaluation of the muscular structure will be carried out using ultrasound images of the participant’s dominant lower limb, which will be captured using Siemens Sonoline Sienna equipment (Issaquah, WA, USA), together with a linear matrix transducer (48 mm, 7, 5 MHz) to determine the thickness of the rectus femoris (RF) and vastus lateralis (VL) muscles. Anatomical reference points and skin marks will be drawn on transparent sheets to ensure similar positioning of the ultrasound transducer in the same location in the evaluations.

The images will be taken between the midpoint of the greater trochanter and the lateral condyle of the femur [46]. The ultrasound transducer will be covered with water-soluble transmission gel and positioned perpendicular to the skin over the RF and VL and oriented parallel to the muscle fascicles [46]. The alignment of the transducer will be considered adequate when several fascicles can be drawn without interruption through the image [46].

